# Effects of relaxation therapy on maternal psychological state, infant growth and gut microbiome: protocol for a randomised controlled trial investigating mother-infant signalling during lactation following late preterm and early term delivery

**DOI:** 10.1186/s13006-019-0246-5

**Published:** 2019-12-16

**Keywords:** Breastfeeding, Maternal stress, Infant growth, Infant behaviour, Relaxation therapy, Gut microbiome

## Abstract

**Background:**

Breastfeeding is of great importance for infant health both short and long term, especially for those born preterm. Apart from the socio-economic and cultural factors which may influence a mother’s decision on breastfeeding, lactation performance is also influenced by maternal physiological and psychological condition, as well as infant behavioural factors. The aim of this project is to investigate physiological, psychological and anthropological aspects of ‘signalling’ between mother and infant during lactation in a stressful situation, following late preterm delivery, using an experimental approach.

**Method:**

A single blind parallel randomised controlled trial will be conducted in Chinese primiparous mothers who deliver a infant (34 0/7–37 6/7) weeks and plan to exclusively breastfeed. Mothers will be recruited from four local community clinics attached to Beijing Children Hospital. Two home visits will be arranged at one week and eight weeks postpartum. Participants will be randomly assigned to either intervention arm or control (no intervention) before the first home visit. Mothers from the intervention group will be asked to listen to an audio recording with relaxation meditation daily during breastfeeding. Maternal stress and anxiety will be measured at one week and eight week postpartum using Chinese version of Cohen’s Perceived Stress Scale (PSS) and Beck Anxiety Inventory (BAI). Infant weight and length gain (as SD scores) from one to eight week will be measured using anthropometry. Milk volume will be measured using 48-h test-weighing method. Breast milk samples and mother and infant’s stool samples will be collected to measure macronutrient and microbiome content. Anthropometric measurements (weight, length and head circumference) will be performed during all home visits.

**Discussion:**

Primary outcomes of this study will be the effect of the intervention on maternal psychological state, and infant growth. Other outcomes will include the effect of the intervention on milk production, infant behaviours, and the microbiome composition in breastmilk and maternal and infant’s gut. Results of this study will provide greater understanding about maternal-infant factors which influence the success of breastfeeding, and which may then be useful targets for future interventions.

**Trial registration:**

ClinicalTrials.gov identifier: NCT03674632. Registered 14 September 2018.

## Background

Early infancy is a critical period of development and has an important impact on long term health and development. Just as the milk of thousands of other mammalian species has been shaped by natural selection for their offspring, human breast milk has been shaped by selection to maximise the reproductive fitness of human mothers, by promoting the survival and fitness of all her offspring [1, 2]. Increasing evidence shows the effects of human breast milk on optimizing infant growth and development, as well as protecting against infection and developing the immune system [1–4]. However, despite a number of health programmes designed to promote breastfeeding, it is widely recognised that the exclusive breastfeeding (EBF) rates in many countries are disappointingly low and resistant to change [2]. Overall, less than half of infants globally are exclusively breastfed for six months, with a global rate of 39% reported by UNICEF (2012) [5]. In rural areas of China, the EBF rate for infants in the first six months was only 28.7% [6].

Apart from the socio-economic and cultural factors which may influence a mother’s decision on breastfeeding, lactation performance is also influenced by maternal physiological and psychological condition, as well as infant behavioural factors [7, 8]. Breastfeeding is a dynamic process that involves complex physiological signalling and behavioural ‘negotiation’ between the mother and the infant. The baby can ‘signal’ its needs to the mother by its behaviour, such as crying, and the mother can respond by allowing or restricting breast access to alter the production of milk. These processes may shape infant behaviour and feeding, and hence may influence infant growth [7].

While a number of attempts to improve breastfeeding rates focus on providing additional support, many aspects of the breastfeeding process remain poorly understood [2, 9]. Moreover, most studies in this area are observational, which makes it difficult to define causal effects of potential ‘signals’. However, a previous study, the MOM study [10], investigated mother-infant signalling during breastfeeding in 58 Malaysian mothers who were breastfeeding their healthy term infant in a randomised controlled trial; maternal psychological state was manipulated in the intervention group using a relaxation meditation tape. The intervention was effective in reducing maternal stress during breastfeeding, favourably affecting breast milk composition and positively influencing infant sleeping behaviour and growth [10]. Compared to the sample population of this study, there might be greater maternal stress for mothers who have a late preterm infant (LPI) or early term infant (ETI), and the expected benefits of the intervention might be greater. Whilst most LPIs and ETIs who are otherwise healthy are able to establish breastfeeding, the situation is likely to be less straightforward than term infant (>38 week) [11], introducing greater stress. This new study will therefore focus on mothers with LPIs and ETIs, using an experimental approach and a larger sample size to further investigate the causal relationships between maternal psychological state and infant outcomes, and to explore signalling between mother and infant during breastfeeding.

In this study, named the Breastfeed a Better Youngster (BABY) Study, we hypothesise that the use of a relaxation therapy by breastfeeding mothers of late preterm or early term infants starting one week postpartum will result in reduced maternal stress and anxiety, greater infant growth, increased total amount of human milk oligosaccharides in breast milk, increased breast milk volume and energy.

In addition, based on recent research, we will investigate the role of the microbiome in mother-infant signalling. The composition of milk microbiota may reflect the mother’s gut microbiome, and in turn influence the microbiome in the infant’s gut [12–14]. Increasing evidence suggests that there is a bidirectional communication between the central nervous system (CNS) and the gastrointestinal tract, which means while the gut microflora can alter the host’s behaviour, the host’s psychological status may also have an influence on modulating the structure of the gut microbiota community [13, 15]. Animal studies using 16S RNA sequencing techniques examined the gut microbiota in male mice/rats and demonstrated that stress can alter the brain-gut axis function and also modifies the relative diversity of the gut microbiota [16, 17]. Studies also supported a role of the gut microbiota in the regulation of stress, emotion, and cognition by using germ-free animals exposed to antibiotic drugs, probiotic bacteria or pathogenic bacterial infections [18–20]. These findings are consistent with the hypothesis that maternal stress during breastfeeding could influence the mother’s gut microbiota, thereby altering the milk microflora, and consequently having an impact on the infant gut microbiota, which could result in changes of infant behaviour (Fig. 1). Thus, the microbiome may play a role in signalling between mother and infant.

**Fig. 1 Fig1:**
[figure not shown]
Hypothesis of the mother-infant signalling. Figure Legend – *EMT* Entero-Mammary Trafficking, *HMO* human milk oligosaccharides

## Methods

### Study design

A single-blinded randomised controlled trial will be conducted in Chinese mothers who deliver an infant (34 0/7–37 6/7 weeks of gestation) and plan to exclusively breastfeed. Mothers will be recruited while they are in the maternity hospital. A baseline assessment will be conducted during the one week postpartum home visit, with another study visit at eight weeks after delivery. After obtaining written informed consent, participants will be randomly assigned to either the intervention arm or control conditions (standard management). Participants will be told that the aim of the study is to investigate factors that may make breastfeeding easier for mothers with an LPI or ETI, so they can breastfeed for longer. They will not be told about the randomisation until the end of the study, as this knowledge would most likely lead to mothers in the control group using some form of relaxation therapy. Background characteristics of mothers and their early feeding experiences will be recorded.

### Hypotheses and outcome measures

#### Primary hypotheses

The use of a relaxation therapy by breastfeeding mothers of LPI and ETI that will be given from one week to eight week postpartum, will result in:
reduced maternal stress and anxietygreater infant growth, specifically increased weight and length gain

Primary outcomes and measures
maternal stress and anxiety at one week and eight week postpartum, measured by Chinese version of Cohen’s Perceived Stress Scale (PSS) and Beck Anxiety Inventory (BAI) respectively.infant weight and length gain (as SD scores) from 1- to 8-week measured using anthropometry.

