### Randomisation and blinding

The baseline assessment will be conducted during the one week postpartum home visit. After recording the demographic characteristics of mothers and their early feeding experience, participants will be randomly assigned to either intervention arm or control conditions (standard management) by randomisation envelope. A member of the research team who will have no contact with participants will produce the randomisation schedule using a computer random number generator, and prepare the assignments in sealed opaque envelopes. Randomisation will be stratified by gestational age (34–35 weeks, 36–37 weeks), delivery mode (vaginal, caesarean), and by the study centre (four community clinics). Participants will not know about the randomisation until the end of the study; they will be aware that the aim of the study is to investigate factors that may make breastfeeding easier for mothers with an LPI or ETI, so they can breast-feed for longer. The researchers will be blinded during the data analysis process; however, they cannot be blinded during data collection since additional materials (diary for recording the use of relaxation tape) will be collected during the data collection period.

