### Other assessments

#### Anthropological measurements on mothers and infants

Mothers and infants will be weighed at the one week and eight week home visit. The weight will be measured to the nearest 0.1 kg using an electronic scale. Anthropometric measures on the infants also include recumbent length and head circumference. Each measure will be repeated three times and the mean value will be used. All measurements will be done following the detailed instructions provided by the World Health Organization instructions on child assessment.

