### Statistical analysis plan

All questionnaires and anthropometric data will be analysed using IBM SPSS (version 24). Intention-to-treat analysis will be performed for comparing primary outcomes (perceived stress and anxiety, infant weight and length gain from baseline to the endpoint) between intervention and control groups at the eight week postpartum using two sample t-test. Paired t-test will be used to compare baseline to post-intervention changes of each primary outcome. The association between the effects of the intervention and the frequency of use will be examined by two-tailed Pearson correlation. Two-sample t-test will be used to compare the changes in milk volume, energy and macronutrients level between intervention and control group. Regression analysis will be used to adjust for confounding factors.

Furthermore, associations between infant temperament/behaviour and the composition of microbiota in mother’s breastmilk, mother and infants’ gut will be examined using univariate ANOVA. Multiple regression analysis and MANOVA will be used to detect differences among significant predictor variables identified by ANOVA.

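### The primary growth outcome is a change in SD score that spans 40 weeks postmenstrual age in every infant, but its main test is unadjusted and the within-arm paired test can reflect the scale rather than growth

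*Protocol article*

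**What the plan says.** Under Hypotheses and outcome measures, the protocol article lists as a primary outcome "infant weight and length gain (as SD scores) from 1- to 8-week measured using anthropometry". Study design enrols mothers who "deliver an infant (34 0/7–37 6/7 weeks of gestation" and times both visits from birth: "A baseline assessment will be conducted during the one week postpartum home visit, with another study visit at eight weeks after delivery".

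The Statistical analysis plan section compares the arms on this gain by intention to treat with a two-sample t-test, and adds: "Paired t-test will be used to compare baseline to post-intervention changes of each primary outcome". It then promises regression to adjust for confounders, without naming any.

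Two other places bear on the point:
- Randomisation and blinding: "Randomisation will be stratified by gestational age (34–35 weeks, 36–37 weeks", alongside delivery mode and study centre.
- The section on anthropometry: "All measurements will be done following the detailed instructions provided by the World Health Organization instructions on child assessment".

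The article does not say which growth reference turns a weight or length into an SD score, or whether age is counted from birth or from the due date.

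**The concern.** An SD score depends on the reference and on the age at which the infant is placed on it. For infants born near their due date, age since birth and age corrected for gestation almost coincide, so the choice matters little. Here they differ by two to six weeks, and the two visits lie on either side of the due date.

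A standard that begins at term birth has no entry for any baseline if age is corrected, because every corrected age is then negative. If age is counted from birth, it returns a score but treats a 34-week and a 37-week infant as equally mature. The shortfall this creates at week 1 need not equal the shortfall at week 8. The difference between the two enters the gain as a component that depends on gestational age.

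Two of the stated analyses are exposed. The unadjusted two-sample t-test counts that component as noise. The paired t-test within each arm has no protection from randomisation, so a drift in the scale would look like a change in the infants.

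**Working it through.** **The plan's own figure.** The only computed sample size is for perceived stress. 16 × 5.00² / 3.13² = 400 / 9.797 = 40.8, so 41 per group and 82 in total, as stated. Nothing is computed for growth, so this figure neither supports nor contradicts the point. The planned total is 120.

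**Timing.** Postmenstrual age = gestational age at birth + age since birth.
- Week 1: 34+0 to 37+6 plus 1 week = 35+0 to 38+6. Relative to 40+0 this is −5.0 to −1.1 weeks.
- Week 8: 34+0 to 37+6 plus 8 weeks = 42+0 to 45+6. Relative to 40+0 this is +2.0 to +5.9 weeks.
- The visits straddle 40+0 for 28 of 28 eligible birth days. This tolerates visit drift: the first visit could be as late as day 14 for an infant born at 37+6, and the second as early as day 42 for one born at 34+0.

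**Size of a gestational-age component, if there is one.** The documents give no growth figures, so these are assumptions: gestational age uniform over four weeks; gain changing by b = 0.1, 0.2 or 0.3 SD per week of gestation; SD of change from other sources s = 0.6 or 0.8.

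The earliest and latest births are 27/7 = 3.86 weeks apart, so their expected gains differ by 0.39, 0.77 or 1.16 SD.

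Variance of gestational age:
- Full range: 4²/12 = 1.333 (SD 1.155 weeks).
- Within a two-week stratum: 2²/12 = 0.333 (SD 0.577 weeks).
- The strata therefore account for 1.000 / 1.333 = 75% of it.

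Inflation = 1 + b² × Var(gestational age) / s². Effective n = 120 / inflation.

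| b | s | Ignoring gestational age | Effective n | Adjusting for the two strata | Effective n |
|---|---|---|---|---|---|
| 0.1 | 0.6 | +3.7% | 116 | +0.9% | 119 |
| 0.1 | 0.8 | +2.1% | 118 | +0.5% | 119 |
| 0.2 | 0.6 | +14.8% | 105 | +3.7% | 116 |
| 0.2 | 0.8 | +8.3% | 111 | +2.1% | 118 |
| 0.3 | 0.6 | +33.3% | 90 | +8.3% | 111 |
| 0.3 | 0.8 | +18.8% | 101 | +4.7% | 115 |

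Adjusting for exact gestational age would remove a linear component altogether.

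**Power.** Take an effect of 0.5 s and 60 per arm, two-sided 5%. With no such component, z = 0.5 × √(60/2) = 2.739, and power = Φ(2.739 − 1.960) = 78%. In the worst row, z = 2.739 / √1.333 = 2.372, and power = Φ(0.412) = 66%. With the strata adjusted for, z = 2.739 / √1.083 = 2.631, and power = Φ(0.671) = 75%. The 66% slightly overstates the loss, because stratified allocation makes the true arm difference less variable than the unadjusted standard error implies.

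**Bias between arms.** In simulated trials of 120 infants, with 1:1 allocation balanced within the two gestational-age strata and the slopes above, the mean difference between arms stayed below 0.01 SD.

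**Paired test.** With 60 infants in an arm, a mean change is significant once it exceeds about 1.96 × s / √60. That is 0.15 SD for s = 0.6 and 0.20 SD for s = 0.8. A scale drift of that size would suffice without any intervention effect.

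**The case against.** The strongest reply is that the premise is not in the article. It nowhere adopts a term-based standard. A reader might infer one from the World Health Organization sentence, but that sentence governs how measurements are taken, not how they are scored. One reference by postmenstrual age at both visits is fully compatible with the text, and a condensed article may leave that choice to the full protocol. This stands: the mis-scoring is conditional, and the missing reference is not itself counted as a fault.

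A reader might also infer that the randomised comparison is biased or invalid. The documents do not support that. Gestational age is a stratification factor, chance imbalance within strata is ordinary random error, and the average bias is about zero whichever reference is used.

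Nor is gestational age necessarily ignored. The promised regression could include it, and the upper figure of 33% applies only to an analysis that ignores both the covariate and the strata.

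Finally, that all visits straddle term depends on taking term as 40 weeks. The Background writes that "the situation is likely to be less straightforward than term infant (>38 week", which implies an earlier boundary. At 38+0 the visits straddle for 21 of 28 birth days, and at 37+0 for 14 of 28.

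What remains is what the article does fix. The main test of a primary outcome is unadjusted, although a strong candidate covariate and the baseline value are both collected. A paired test is also applied to an outcome whose zero point may move between visits.

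**Conclusion.** The point holds as a matter of precision and interpretation. The growth gain spans 40 weeks postmenstrual age for every eligible infant, and the stated t-tests take no account of gestational age. The between-arm comparison remains unbiased on average.

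If the scores carried a gestational-age component, variance would rise by about 2 to 33% with gestational age ignored, and by about 0.5 to 8% with the strata adjusted for. Those ranges rest on assumed slopes of 0.1 to 0.3 SD per week, an SD of change of 0.6 to 0.8 and a uniform spread of gestational age, none of which is in the documents. With a reference indexed by postmenstrual age the component could be small or absent.

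The within-arm paired change is the weaker of the two analyses, because a non-zero result could come from the scale alone. The article does not say that this change will be read as an intervention effect, so the risk is one of interpretation.

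**What to change.** - **Outcome definition.** State that weight and length SD scores at both visits are computed by sex and exact postmenstrual age, from one reference valid from 35 to 46 weeks.
- **Between-arm analysis.** Replace the unadjusted t-test for growth with a regression of the 8-week value on arm, 1-week value, exact gestational age, sex and exact age at visit, together with the randomisation strata. Name these covariates in advance in place of the general reference to confounders. With 120 infants and 2 × 2 × 4 = 16 stratum cells, enter the stratification factors as main effects.
- **Paired test.** Report the within-arm change in SD score as descriptive only.

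The cost is wording. Gestational age is already needed for eligibility and stratification, the 1-week value is already measured, and sex and visit dates should be on record. Settling the reference before the arms are compared also avoids choosing it after the results are seen. The small downside is that the scores are less directly comparable with those from studies of term infants.

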#### Secondary hypotheses

The use of a relaxation therapy by breastfeeding mothers of LPI and ETI from one week to eight week postpartum will result in increased breast milk volume, energy carbohydrate and total amount of HMO in breast milk.The use of a relaxation therapy by breastfeeding mothers of LPI and ETI from one week postpartum will have a positive effect on maternal attitudes toward breastfeeding and infant eating behaviour.The composition of microbiome in vaginally delivered infant’s gut and their mother’s milk is associated, and this will be altered by the intervention, with effects on infant appetite, behaviour and temperament.

Secondary outcomes and measures
energy content of breast milk at eight weeks, calculated by milk intake assessed using test weighing methods [21].composition of macronutrients, specifically the lactose and HMO in breast milkcomposition of breast milk microbiota, maternal and infant gut microbiota, measured by the 16S rRNA based amplicon sequencing techniqueinfant appetite at eight week, three month, and six month, assessed using the Baby Eating Behaviour Questionnaire (BEBQ) [22].maternal feeding attitudes at eight week, three month, and six month, measured using the IOWA Infant Feeding Attitudes Scale (IIFAS) [23].infant behaviour, measured by three day infant behaviour diary at eight week.

### Study population and recruitment

The study population will be recruited from four local community clinics located in different districts of Beijing. The target sample population is Chinese primiparous mothers with a singleton pregnancy who are breastfeeding their LPI or ETI. Eligible mothers (Table 1) will be approached 2–3 days after delivery when they stay at the hospital and breastfeeding is successfully established. The information sheet will be provided to mothers who are interested. A research assistant will explain the outline of the study but will not mention the randomisation. Mothers will be asked to read through the information sheet carefully and discuss with their family.

**Table 1 Tab1:** Eligibility criteria for mother and infant

Inclusion criteria	
Chinese primiparous mothers	
Singleton pregnancy	
Free from any disease that will influence breastfeeding	
Non-smoker	

After discharge from the hospital, the parents will be contacted by the local clinic to see if they are interested in taking part and the first home visit for baseline assessment will be scheduled at the one-week postpartum follow-up. Eligible participants will be asked to sign the consent form. All questionnaires and the information sheets are in Chinese. An overview of this study is provided in Fig. 2.

